#### Secondary lung function outcomes

Spirometry at enrolment and 6 and 12 months after the second vaccine dose.

#### Secondary safety outcomes

Local injection site and systemic reactions in the 7 and 30 days following each vaccine dose, respectively, and SAEs throughout the entire study period.

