### Eligibility

*Inclusion criteria* are:

1. Aged 18 months to 14 years inclusive with recurrent PBB, CSLD or bronchiectasis.

2. Receipt of meningococcal C conjugate vaccine at least six months before enrolment;

3. Negative urine pregnancy test if post-menarchal female.

4. Provision of written informed consent from parent/guardian (assent if child aged ≥10 years).

5. Parent/child willing and able to meet the requirements of the protocol.

6. Access to a telephone and not planning to move from the study area in the 14 months post-enrolment.

7. Has experienced two or more respiratory exacerbations in the 18 months prior to study entry.

*Exclusion criteria* are: chronic lung conditions other than co-existent asthma and those under investigation in this study; prior vaccination with PHiD-CV vaccine; received the 23-valent pneumococcal polysaccharide vaccine (Pneumovax-23, Commonwealth Serum Laboratories Biotherapies, Melbourne, Victoria, Australia) within the previous two months; contraindication/known hypersensitivity to PHiD-CV and/or quadrivalent (ACYW_135_) meningococcal conjugate vaccine; immunosuppressive condition or immunodeficiency disorder that may influence responses to vaccines; systemic immunosuppressive therapy; administration of immunoglobulins and/or blood products within 90 days of receiving study vaccine; active participation in a clinical trial of another investigational drug/vaccine or therapy; acute illness at the time of enrolment, and other medical conditions that could increase the risk of serious adverse events (SAEs) from being in the study.

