### Intervention, follow-up and data collection

Children will be randomised (1:1 allocation) to receive either PHiD-CV or meningococcal (ACYW_135_) conjugate vaccine. Following baseline assessment of their general medical history, respiratory status (including spirometry for children aged ≥6 years), concomitant medication use and vaccination history, children will receive two vaccine doses, 2 months apart, and followed for 12 months post the second vaccine dose. Follow-up includes: three further clinical visits (1, 6 and 12 months post-dose-2); fortnightly telephone interviews with parents to monitor respiratory status; local and systemic adverse event monitoring using parent-completed daily diary cards for 7 and 30 days, respectively, after each vaccine dose; and surveillance for SAEs for the entire study period. All data will be recorded on standardised forms. The primary and secondary outcome measures are collected at the time points specified in Figure 1.

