### Outcome measures

#### Primary outcome

The incidence of respiratory exacerbations in the 12 months following the second vaccine dose.

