#### Secondary analyses

The proportion of children with nasopharyngeal carriage of *H. influenzae* and *S. pneumoniae* at each time point will be compared between vaccine groups and presented as RR and 95% CI, adjusted for repeated measures. VE (%) against carriage will be calculated as (1-RR)*100 and presented with its 95% CI. Bacterial load at each time point will be compared.

Serum and mucosal antibody responses to *H. influenzae* proteins, including PD, pneumococcal protein and polysaccharide antigens and opsonophagocytic killing assays: geometric mean titres at each sampling time point will be compared between groups presented as a mean difference (and 95% CI) from linear regression models. In addition, the proportion of children assessed to be seropositive will be compared between groups at each sampling time point using χ^2^ tests for proportions and logistic regression models to adjust for stratification. All differences will be presented with their 95% CIs.

Safety and reactogenicity of vaccination: descriptive analyses will be performed on the number, type and severity of local and systemic reactions and SAEs that occur following vaccination and presented by treatment group. Comparisons between groups will be performed using Student’s *t*-test for continuous variables and χ^2^ tests for proportions.

Sub-group analyses will be performed for all primary and secondary objectives to examine potential differences by study specific strata. Univariate and multivariate analyses will be performed to evaluate variables independently associated with study endpoints and to assess potential confounding factors in the association between vaccination and disease.

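### Systemic reactions are compared over 30 days after each dose with no early window separated, so background illness can dilute an early vaccine-related excess

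*Protocol article*

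**What the plan says.** Under Secondary safety outcomes, the protocol article lists "Local injection site and systemic reactions in the 7 and 30 days following each vaccine dose, respectively", together with SAEs throughout the study. Intervention, follow-up and data collection describes the source as "local and systemic adverse event monitoring using parent-completed daily diary cards for 7 and 30 days, respectively, after each vaccine dose". Systemic events are thus recorded day by day, and the article gives no rule for attributing them to the vaccine.

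Under Secondary analyses, "descriptive analyses will be performed on the number, type and severity of local and systemic reactions and SAEs that occur following vaccination", presented by treatment group. The section then goes beyond description: "Comparisons between groups will be performed using Student’s" t-test for continuous variables and χ² tests for proportions. No systemic window shorter than 30 days is named.

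Two other parts of the article bear on this. The eligibility criteria require that the child "Has experienced two or more respiratory exacerbations in the 18 months prior to study entry". The primary outcome is "The incidence of respiratory exacerbations in the 12 months following the second vaccine dose", so the 30-day diary period after dose 2 lies wholly inside the efficacy period.

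**The concern.** A reaction caused by an injection would be expected mostly in the first days. Counting systemic events over 30 days adds about three further weeks in which, in this population, much of what parents record may be ordinary illness. That illness raises the event proportion in both arms. A child who would have been ill anyway cannot add to the excess, so the between-group difference shrinks while its variance grows.

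After dose 2 there may be a second effect. If PHiD-CV reduces respiratory illness from the start of the efficacy period, and if the diary counts such illness, the PHiD-CV arm has less background. This works against any excess of early reactions in that arm.

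What is at stake is the fourth secondary objective, the safety of both vaccines. The Discussion says a complete safety evaluation is intended because the vaccines are used outside licensed indications in children with existing morbidity. A finding of no difference in systemic reactions over 30 days could be reported although a difference existed in the first week.

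**Working it through.** The article gives no power or precision figure for the safety comparison, so there is none to reproduce. The check uses the article's exacerbation rates to gauge background illness.

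**Inputs from the article**
- Control rate 2.1 exacerbations per year; target rate 2.1 × 0.70 = 1.47 (Sample size).
- 103 children per group recruited; two-sided 5% level (Sample size).
- Windows of 7 and 30 days (Secondary safety outcomes).

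The Poisson formula with these rates, (1.960 + 1.282)² × (2.1 + 1.47) / 0.63², gives 94.5 per group. The article states 93, so the rates are read as intended.

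**Step 1: chance of at least one exacerbation in a window**

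P = 1 − exp(−rate × days / 365.25)

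| Window | 2.1 per year | 1.47 per year | Difference |
|---|---|---|---|
| 30 days | 1 − exp(−0.1725) = 15.8% | 1 − exp(−0.1207) = 11.4% | 4.5 points |
| 7 days | 1 − exp(−0.0402) = 3.9% | 1 − exp(−0.0282) = 2.8% | 1.2 points |

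(Differences are taken before rounding.) The difference column is the most that efficacy alone could remove from the PHiD-CV arm after dose 2 at these rates. It assumes that every exacerbation counts as a systemic event and that the full 30% effect acts from the first day.

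**Step 2: effect on an assumed reaction excess**

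Assumption, not in the article: true systemic reaction risks of 10% (control vaccine) and 20% (PHiD-CV), all within 7 days and independent of background illness. Then P(any event) = 1 − (1 − reaction risk) × (1 − background). Power is for a two-proportion test with 103 per group. With no background illness at all it is 52%.

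| Window | Effect on illness | Control | PHiD-CV | Difference | Power |
|---|---|---|---|---|---|
| 30 days | none | 24.3% | 32.7% | 8.4 points | 27% |
| 30 days | 30% reduction | 24.3% | 29.1% | 4.8 points | 12% |
| 7 days | none | 13.6% | 23.2% | 9.6 points | 43% |
| 7 days | 30% reduction | 13.6% | 22.2% | 8.7 points | 37% |

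The rows with no effect on illness show dilution alone, which can apply after either dose. The other rows can apply only after dose 2.

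**Step 3: sensitivity to the background rate**

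The 2.1 per year counts only episodes that led to hospital clinic attendance or admission. The trial's own definition is symptom-based, so diary-recorded illness may be more frequent. With the same assumed reaction risks and a 30% reduction in illness, the 30-day difference is 0.9 points at 4.2 per year and −2.1 points at 6.3 per year (both rates assumed). The matching 7-day differences are 7.4 and 6.2 points. Conversely, if diary items pick up little respiratory illness, the efficacy offset is close to nil.

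**The case against.** The strongest reply is that the 30-day period is an observation window, not a defined composite. The article describes reactions by number, type and severity, so fever or irritability could be examined apart from respiratory illness. Nothing says that an exacerbation is a systemic reaction: exacerbations have their own definition and are captured by fortnightly telephone contact and parent report. This stands, and it means the percentages in Step 1 are exacerbation risks used as a stand-in, not predicted systemic-reaction rates. Tabulating by type does not, however, separate early from late onset, and non-respiratory symptoms can also arise from intercurrent illness.

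Second, the control is an active conjugate vaccine. A calculation that lets it cause no reactions exaggerates the gain from a short window. With 10% reactions in the control arm, even the 7-day comparison has modest power (37% to 43%). This also stands.

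Third, the long window serves the stated aim of a complete safety evaluation, and the article says its endpoints match those used in trials of both vaccines. That is a good reason to keep the 30-day result. It is no reason to leave the early days unseparated, and it does not address background illness in these children.

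Fourth, finer tabulation can be left to an analysis plan. That is true of layout, but the windows and the between-group tests are fixed in the article itself.

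A reader might go further and infer that efficacy and harm oppose each other throughout the safety outcome, or that the 30-day comparison should be demoted to description. The documents support neither. The offset is confined to the period after dose 2 and depends on early protection and on what the diary records. After dose 1 the issue is at most dilution, and excluding acutely ill children at enrolment should lower the early background.

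**Conclusion.** The point holds in a limited form. Comparing systemic reactions over 30 days after each dose, with no early window separated, makes the comparison less sensitive to an early vaccine-related excess than the planned data allow. Dilution by unrelated illness follows from the stated window and population. The efficacy offset is conditional: after dose 2 only, and only if diary items capture respiratory illness and protection begins within the first month. At the article's planning rates it would be about 4.5 points over 30 days against about 1.2 points over 7 days.

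In the illustration with assumed reaction risks of 10% and 20%, power is 27% (30 days) against 43% (7 days) from dilution alone, and 12% against 37% with the offset added. These figures show direction and rough scale; they are not estimates for this trial. The primary analysis and SAE surveillance are unaffected, and because diaries are daily the problem is fully recoverable.

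**What to change.** In Secondary safety outcomes and in the safety paragraph of Secondary analyses, pre-specify before unblinding:

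- a between-group comparison of systemic reactions in days 0–6 after each dose, by type, matching the length of the local-reaction window;
- separate reporting of days 7–29 after each dose;
- the full 30-day result, retained as planned.

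No new visit, form or data item is needed, because the daily diaries already hold the information. The cost is one additional secondary safety comparison. Fixing the window in advance also avoids a choice made after the data are seen.

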### Sample size

Prospective data collected in Brisbane children with non-CF bronchiectasis indicate a mean annual incidence of 2.1 (standard deviation 1.046) exacerbations requiring hospital clinic attendance or hospitalisation. PHiD-CV efficacy against exacerbations in children with bronchiectasis is unknown. However, based on the aforementioned pilot data and AOM data from the POET study (30% reduction) [33], our trial is powered to detect a 30% reduction from 2.1 to 1.47 exacerbations in the 12 months following the second vaccine dose. Assuming a Poisson distribution, 93 children per group will provide 90% power (α = 0.05, two-sided) to detect a 30% reduction in exacerbations in the PHiD-CV group and 80% power to detect a 25% reduction. Assuming a 10% loss to follow-up, we will recruit 206 children (103 per group). Differences of less than 20% are unlikely to change clinical practice without additional supporting evidence.

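### With 93 children per group the power for a 25% reduction is about 75%, not the stated 80%

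*Protocol article*

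**What the plan says.** The Sample size section of the protocol article takes from pilot data a "mean annual incidence of 2.1 (standard deviation 1.046) exacerbations" and sets the design effect as a "30% reduction from 2.1 to 1.47 exacerbations in the 12 months". Its power statement begins "Assuming a Poisson distribution, 93 children per group", with "90% power (α = 0.05, two-sided") for the 30% effect. The same sentence then adds "80% power to detect a 25% reduction". Loss to follow-up enters only afterwards: "Assuming a 10% loss to follow-up, we will recruit 206 children (103 per group"). Both power figures therefore belong to 93 children per group, not 103.

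The section closes by saying that differences below 20% would probably not alter practice unless other evidence supported them. The Analysis section confirms that the primary comparison of incidence assumes a Poisson distribution.

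**The concern.** The sentence gives two power figures for one sample size, one distribution and one α. Once the first is fixed, the second follows from it. Moving from a 30% to a 25% reduction at constant sample size should cost more power than the ten points the plan allows.

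The 25% figure is the only assurance the plan gives for an effect smaller than its design effect. Since the plan treats reductions under 20% as unlikely to change practice by themselves, a reader of a null result will want to know how often a true effect between 20% and 30% would be missed. At 25% the plan implies one trial in five. On its own inputs it is one in four.

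**Working it through.** **Inputs, all stated in the article.** Control rate λ₀ = 2.1 per child-year; Poisson counts; two-sided α = 0.05, so the critical value is 1.960; n = 93 evaluable per group (Sample size). Allocation is 1:1 (Intervention, follow-up and data collection). Follow-up for the outcome is 12 months (Primary outcome). The treated rate is λ₁ = 2.1 × 0.70 = 1.47 for a 30% reduction and 2.1 × 0.75 = 1.575 for a 25% reduction.

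**Formulas.**
- Log rate ratio: power = Φ(|ln(λ₁/λ₀)| / √(1/(nλ₀) + 1/(nλ₁)) − 1.960)
- Rate difference: power = Φ((λ₀ − λ₁) / √((λ₀ + λ₁)/n) − 1.960)
- Square root: power = Φ(2(√λ₀ − √λ₁) / √(2/n) − 1.960)

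**Step 1: the 30% figure reproduces.** On the log scale, |ln 0.70| = 0.3567 and SE = √(1/195.3 + 1/136.71) = 0.1115. The ratio is 3.199 and power is Φ(1.239) = 89.2%. On the difference scale, 0.63/√(3.57/93) = 3.216, so power is Φ(1.256) = 89.5%.

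**Step 2: the 25% figure does not.** On the log scale, |ln 0.75| = 0.2877 and SE = √(1/195.3 + 1/146.475) = 0.1093. The ratio is 2.632 and power is Φ(0.672) = 74.9%. On the difference scale, 0.525/√(3.675/93) = 2.641, so power is Φ(0.681) = 75.2%.

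| Method, 93 per group | 30% reduction | 25% reduction |
|---|---|---|
| Stated in the plan | 90% | 80% |
| Log rate ratio (Wald) | 89.2% | 74.9% |
| Rate difference | 89.5% | 75.2% |
| Square root | 89.8% | 75.4% |
| Log rate ratio, pooled null variance | 89.8% | 75.6% |
| Exact conditional test | 88.7% | 73.7% |
| Simulation, 1,000,000 trials (Wald, likelihood-ratio and score tests) | 89.7–89.8% | 75.3–75.5% |

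**Step 3: consistency within the sentence.** Suppose power for the 30% effect is exactly 90%. The expected test statistic is then 1.960 + 1.282 = 3.242. Rescaled to the 25% effect on the difference scale, it becomes 3.242 × (0.525/0.63) × √(3.57/3.675) = 2.66, and Φ(2.66 − 1.96) is about 76%. Granting the plan its 90% still leaves the second figure about four points short.

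**Step 4: sample size needed for 80% at 25%.** With (1.960 + 0.842)² = 7.849:
- Difference scale: 7.849 × 3.675/0.525² = 104.7, so 105 per group.
- Log scale: 7.849 × (1/2.1 + 1/1.575)/0.2877² = 105.4, so 106 per group.

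Allowing for 10% loss, this means recruiting 117 to 118 per group (105/0.9 and 106/0.9). With 93 per group, the log-scale formula reaches 80% power at a reduction of 26.5%.

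**Step 5: other readings tried.**
- All 103 recruited children evaluable: 79.1% to 79.7% for the 25% effect by the log-rate, difference and square-root formulas.
- Final nominal level of 0.0497: 74.8%.
- One-sided α (log-rate, difference and square-root formulas): about 84% for 25%, but 94% for 30%.
- Comparison of means with the pilot SD of 1.046: 92.8% for 25% and 98.4% for 30%.
- Comparison of means with SD √2.1: 69.5% for 25% and 84.2% for 30%.
- Signorini approximation, null variance at the control rate: Φ((0.2877 − 1.960 × √(2/195.3))/0.1093) = 79.3% for 25%, and 92.2% for 30%.

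None of these gives both stated figures to within two percentage points.

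**The case against.** The strongest defence is that the 80% is the output of a recognised method and not a slip. The Signorini approximation for Poisson regression, with the null variance evaluated at the control rate, gives 79.3% at 93 per group, which rounds fairly to 80%. It also requires 62.4, hence 63, children per group for 80% power at a 30% reduction, which is the interim figure in the Efficacy stopping rule. Two of the plan's three power figures would then share a source, and the third would be conservative, at 92.2% against a stated 90%.

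This may well explain the origin of the figure. It does not make it correct. The approximation evaluates the null variance at the higher rate, which understates that variance when the treatment lowers the rate. Simulation of the Poisson comparison gives 75.3% to 75.5%.

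Three further objections bear on weight, and they stand in part:
- The shortfall at 103 per group is under one point, so little should be made of the claim failing there. But the plan ties the figure to 93 and expects 10% loss.
- The pilot SD of 1.046 is below the Poisson value of √2.1 = 1.449 and would give higher power. But the plan explicitly assumes Poisson, and that SD gives about 93%, not 80%.
- The 25% clause sizes nothing. The figures 93, 103 and 206 all rest on the 30% effect. This is correct and limits the importance of the point.

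**Conclusion.** The stated 80% is wrong on the plan's own inputs. With 93 evaluable children per group, power for a 25% reduction is about 75%, roughly five points lower, so the chance of missing such an effect is about 25% and not 20%. The effect detectable at 80% power is a reduction of about 26.5%.

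The result assumes Poisson variance, a control rate of 2.1 per year, a full year of follow-up and a two-sided α of 0.05, all as the plan states. A different true variance would move it in either direction. The 90% power for a 30% reduction is sound, so neither the sample size nor the primary analysis is affected. This is a minor correction to a secondary statement.

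**What to change.** Restate the power sentence in the Sample size section along these lines: *with 93 evaluable children per group, power is 90% for a 30% reduction and about 75% for a 25% reduction; 80% power corresponds to a reduction of 26% to 27%.* Naming the formula used would let readers reproduce both figures.

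At the same time, recheck the interim statement in the Efficacy stopping rule, which gives 80% power for a 30% reduction with 63 per group. The formulas that reproduce the plan's 90% give about 75% there too (74.9% by log rate ratio, 75.4% by rate difference).

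The cost is one reworded sentence, plus a second if the interim figure is also corrected. Recruitment, follow-up and the analysis stay as they are. The only loss is a slightly less favourable figure for a 25% effect.

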### Analysis

Data will be presented in accordance with the updated CONSORT criteria [43]. Demographic data will be tabulated and expressed as proportions and/or means of the selected characteristics by vaccine group with the corresponding 95% confidence intervals. Differences between groups will be assessed by the normal test for comparisons of means and χ^2^ tests for comparison of proportions.

The primary analysis will assume a Poisson distribution and will compare the incidence of respiratory exacerbations between the two groups. Vaccine efficacy (VE) (%) will be calculated as (1 – Relative Risk (RR))*100 where RR represents the ratio of the incidence of exacerbations in the PHiD-CV group to the incidence in the control group (and presented with its 95% CI). All analyses will be performed on an intention-to-treat basis and will account for baseline stratification.

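### The primary Poisson analysis states no allowance for a variance that differs from the mean, and the plan's only standard deviation does not match that assumption

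*Protocol article*

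**What the plan says.** The Analysis section of the protocol article fixes the distribution for the one confirmatory comparison: "The primary analysis will assume a Poisson distribution and will compare the incidence of respiratory exacerbations between the two groups". The result is a ratio of incidences, turned into vaccine efficacy with a 95% confidence interval. All analyses are by intention to treat and take account of the randomisation strata, which are site, age below or from six years, and recurrent PBB versus CSLD/bronchiectasis.

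The Sample size section uses the same distribution: "Assuming a Poisson distribution, 93 children per group will provide 90% power (α = 0.05, two-sided) to detect a 30% reduction in exacerbations". The effect is given as follows: "our trial is powered to detect a 30% reduction from 2.1 to 1.47 exacerbations in the 12 months following the second vaccine dose". The control rate comes from Brisbane children with non-CF bronchiectasis, who had a "mean annual incidence of 2.1 (standard deviation 1.046) exacerbations requiring hospital clinic attendance or hospitalisation".

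Neither section mentions a dispersion parameter, a robust variance or a negative binomial model. The Secondary analyses section does adjust the carriage comparisons for repeated measures. No comparable provision is stated for repeated exacerbations in the same child.

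**The concern.** A Poisson model takes the variance of a count to be equal to its mean. The standard error of the log rate ratio then depends only on the number of events, and it is correct only if the variance/mean ratio is 1. The one SD that the plan quotes does not give a ratio of 1.

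The trial's own endpoint may depart from 1 in either direction. The trial enrols children aged 18 months to 14 years with three diagnoses in three cities. Entry requires at least two exacerbations in the previous 18 months, with no upper limit. If children differ in underlying risk beyond what the strata explain, the variance exceeds the mean. The interval for vaccine efficacy is then too narrow and the test rejects too often. If the ratio is below 1, the interval is too wide and the test is conservative.

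The same test is used at the interim analysis, where the nominal boundary is P = .001 and the result informs whether recruitment continues.

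**Working it through.** **Inputs from the protocol article.** Control rate 2.1 per year, SD 1.046, vaccine rate 1.47 (rate ratio 0.70), 93 per group, two-sided α 0.05, 90% power (Sample size section). Interim boundary P = .001 (Efficacy stopping rule).

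**Inputs that are assumed.** Ratios φ = variance/mean above 1. The article gives none. Each φ is to be read as what remains after stratum adjustment.

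**1. Reproduce the stated size.** With φ = 1 and one year per child:

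- Difference in rates: n = (1.960 + 1.282)² × (2.1 + 1.47) / (2.1 − 1.47)² = 10.507 × 3.57 / 0.3969 = 94.5 per group.
- The square-root scale gives 93.8 and the log rate ratio gives 95.5.
- Power at 93 per group is 89% to 90% on all three.

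The 93 per group therefore reproduces within rounding, and it rests on variance = mean. A comparison of means with the quoted SD gives n = 2 × 10.507 × 1.046² / 0.63² = 57.9, that is 58 per group. The quoted SD was not used.

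**2. Compare the quoted SD with Poisson.** Variance = 1.046² = 1.094, so φ = 1.094 / 2.1 = 0.52. A Poisson count with mean 2.1 has SD √2.1 = 1.449.

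**3. True type I error of the plain Poisson test.** α(φ) = 2 × [1 − Φ(z/√φ)], with z = 1.960 for the nominal 5% and 3.291 for the interim .001.

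**4. Valid power for a 30% reduction, 93 per group.** There are two ways to carry φ into the vaccine group:

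- (a) The same φ in both groups: SE² = φ × (1/2.1 + 1/1.47) / 93.
- (b) The same gamma spread of risk in both groups, so the vaccine-group ratio is 1 + 0.7(φ − 1). At φ = 2 this is 1.7, and SE² = (2/2.1 + 1.7/1.47) / 93 = 0.0227. Then 0.357 / 0.151 − 1.96 = 0.41, which gives 66%.

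| φ | True α at nominal 5% | True α at nominal .001 | Power (a) | Power (b) | n per group for 90% under (a) |
|---|---|---|---|---|---|
| 1.0 | 5.0% | 0.1% | 89–90% | same | 95 |
| 1.25 (assumed) | 8.0% | 0.3% | 82% | 83% | 119 |
| 1.5 (assumed) | 11.0% | 0.7% | 74–75% | 77% | 142 |
| 2.0 (assumed) | 16.6% | 2.0% | 62% | 66% | 190 |

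**5. At the quoted ratio of 0.52.** True α is about 0.7%. The interval is too wide by 1/√0.52 = 1.39, that is 39%. The plain Poisson test has about 96% power and a variance-corrected test about 99%.

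**6. Check by simulation.** In 30,000 trials with 93 per group and no strata, the plain Poisson test rejected in 7.8%, 10.9% and 16.5% of null trials at φ = 1.25, 1.5 and 2.0. With a robust variance it rejected in 5.1% to 5.2%. With under-dispersed counts (realised φ 0.475) the figures were 0.5% for plain Poisson and 5.0% for robust.

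**The case against.** The strongest objection is about direction. A reader might infer that the quoted SD shows the primary interval will be too narrow. It does not. Differences in risk between children push the ratio above 1, and the quoted SD puts it at about one half. At that ratio the plain Poisson test is conservative and still has about 96% power. Every anti-conservative figure above depends on a ratio that the article does not supply. This stands in full.

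Nor can the quoted SD be turned round to claim that the trial endpoint is under-dispersed. The article gives no observation time per child. If the annual rates were averaged over about 1.9 years (2.1 / 1.094 = 1.92, an assumption), a pure Poisson process would produce this SD; longer observation would imply over-dispersion. The pilot also covered bronchiectasis only and counted hospital-attended events. The trial counts symptom-defined exacerbations and includes recurrent PBB and CSLD.

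Second, the strata are some of the obvious sources of heterogeneity, and the analysis accounts for them. The requirement for two prior exacerbations also removes some low-risk children. Both reduce the ratio that matters, by an unknown amount, and neither makes it 1.

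Third, this is a condensed article. Poisson regression with a sandwich or scaled variance is often still called Poisson, and an unseen analysis plan may specify it. This lowers the severity. It does not remove the point, because the article itself names the distribution, sizes the trial on it, and quotes beside it an SD that does not fit.

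**Conclusion.** The point holds in a limited form. The primary analysis and the sample size both rest on variance equal to the mean, no allowance for a different variance is stated, and the only SD quoted (ratio 0.52) was neither used nor consistent with that assumption. The dispersion of the trial's own endpoint is unknown in both directions.

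The size depends on the residual ratio. Between assumed values of 1.25 and 2.0, the true type I error of a plain Poisson test runs from about 8% to 17%, and valid power for a 30% reduction from about 82% down to 62–66%. At 0.52 the error is a loss of precision. These figures assume that model-based Poisson standard errors are used, that each child contributes one year, and that 93 children per group are analysed.

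The documents do not support saying that the primary result will be wrong, or that over-dispersion has been shown. Severity: should-fix. Confidence: moderate.

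**What to change.** - **Primary model.** Keep the log-link Poisson rate model with the stratification factors and a log(person-time) offset. Prespecify a robust (sandwich) or scaled variance for the confidence interval and P-value, at the interim as well as the final analysis. Either variance allows for a ratio above or below 1.
- **Sensitivity analysis.** Add negative binomial regression.
- **Sample size section.** State that the 93 per group rests on variance equal to the mean and not on the quoted SD. Give the observation time per child behind that SD if it is known. Show power over a range of ratios, for example 0.5, 1.0, 1.5 and 2.0.

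The cost is wording in the protocol and analysis plan, to be settled before unblinding. No extra data are needed. The downside is that, if over-dispersion is present, the interval will be wider and the stated power less favourable.
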